#### 2.6.1. Nordic Walking (NW)

NW sessions will be performed in a nature park, which offers pathways of different lengths and levels of difficulty. Walking sticks will be provided by the coach to participants. As in our previous study [27], the coach will progressively increase the level of difficulty over the 8 weeks, trying to individualize, as far as possible, the requested effort level while managing the whole group in the nature park. The participants will be following the coach, who shows the way and adapts the walking speed and difficulty.

#### 2.6.2. Conventional Circuit Training (CT-c)

The CT-c protocol will start with a 5 min warm-up for muscle activation and stretching (to avoid articular and muscle injuries); 20 min of aerobic exercises to fully stimulate the aerobic metabolism; 30 min of circuit training divided into different stations (see below the detailed description) to be repeated 2 times; and a 5-min cool-down.

Circuit training stations will be organized in eight successive training stations dedicated to: (i) cardio-vascular exercises (2 different stations), (ii) muscular resistance exercises (2 different stations), (iii) balance, stepping, interlimb, and whole-body coordination exercises (2 different stations), and (iv) motor-cognitive dual-tasks exercises (2 different stations) (see Figure 2).

Cardio-vascular effort is achieved through stepping exercises, using ladder drills, or doing a slalom around gym cones by walking as fast as possible. Muscular resistance training is composed of upper limb and lower limb, flexion-extension exercises performed using body weight and light dumbbells. Balance training is composed of: (i) static exercises carried out in equilibrium of one leg on firm ground or a foam support, with eyes open or closed, and (ii) dynamic exercises, for instance, walking along a straight line or curve drawn on the ground. Coordination training consists of field exercises adapted from current research paradigms (e.g., see [41,42,43]) and previous works (e.g., see [44,45,46]). Specifically, participants perform asynchronous bimanual movements, ipsi- and contralateral arm-leg movements iso-directional or aniso-directional or four-limb coordination patterns while sitting. Dual-task training consists of counting backward, or making some easy math calculations, repeating words backward, finding words of the same family (e.g., all possible vegetables, fruits, animals), or words starting with the same syllable while performing balance, stepping, normal walking, slalom walking or, interlimb coordination tasks.

The participants will work together by pairs, distributed over the different stations, thereby allowing social interactions. Each pair starts working on one station and then goes to the next, in a predetermined order. The order of the stations will be changed every week. For each station, the two participants perform the exercises one after the other, so that working time (e.g., 45 s), plus 15 s dedicated to the stations switch of each member of the pairs, represents a rest time (75 s) for the other one. The exercise session workload is increased approximately every 2 weeks.

#### 2.6.3. Fitlight Trainer™ Circuit Training (CT-fit)

A circuit training (CT-fit) associating cognitive and motor requirements in gamified exercises will be conceived, thanks to a fitness gaming technology (Fitlight Trainer™). The Fitlight Trainer™ is specifically designed to enhance cognitive load during physical exercises, by loading executive functions, reactivity (reaction time), movement velocity, movement accuracy, visuospatial capacities, and spatial memory while physically exercising. Practically, the Fitlight Trainer™ is a gaming technology composed of 24 different lamps that can light up in different colors and is equipped with a proximity and touch sensor wirelessly connected to a tablet. It includes wireless, RGB LED-powered lights, used as target switches, which can be turned-off by participants in a specific order, with upper and/or lower limbs, eventually requiring whole-body complex coordinated movements performed under time pressure. Thanks to the remote-control system on the tablet, various training conditions can be proposed by changing the number of colors of the target switches. Additionally, it depends also on whether the targets are placed on the ground, fixed on a wall or poles (see https://www.Fitlighttraining.com). Thus, this device allows training whole-body complex motor skills, manipulating the level of difficulty of their cognitive requirements and the intensity and duration of the physical exercises. In particular, it allows creating MwT exercises, that require the use of executive functions, visuospatial capacities, reaction time, working memory, and inhibition to succeed in the motor task. To do this, in the present experiment, the 24 lamps are divided into 4 groups of 6 lamps, each group being dedicated to one station. For each group of 6 lamps, we use a specific program proposed by the Fitlight trainer™ (the visuomotor program), which is based on random lighting of 1 to 6 possible different colors (red, blue, light blue, green, yellow, and magenta) during a fixed time period (e.g., 45 s), which represent the time allowed for completing the response. The use of different colors is a means to make the cognitive and motor component embodied one to another. For instance, by choosing two colors from 6 (e.g., red referring to the left hand and blue to the right one), the participant has to inhibit all the automatic responses when a lamp is turned on and to discriminate the color lightened and perform the corresponding motor response. Then, a number of parameters can be set, for instance, the distance of impact (i.e., how strong the impact has to be to turn it off), the time elapsing between the switch-off of one light and the random lightning of another one, and, finally, the type of lightning, static, or flashing. Notably, the program will allow each participant to personalize their movement speed and strategy to execute the cognitive-motor task properly. As with the CT-c, the CT-fit will start with a 20 min aerobic workload, then alternate stations of aerobic, muscular resistance, coordination, balance, and stepping exercises, which generally will involve the same muscle groups and physical effort of the CT-c. However, stations dedicated to dual-task training (i.e., TwM) in the CT-c will be replaced by stations dedicated to MwT training conditions (see Figure 3).

### 2.7. Data Collection and Outcome Measures

Cognitive performance, muscular force, cardiovascular and motor fitness will be assessed before and after the 8 weeks of training. Data collected with the heart rate monitors will be also analyzed, in order to estimate the average intensity of the training interventions (see [27], for a similar procedure).

### 2.8. Cognitive Assessment

Global cognitive status will be evaluated through the Montreal Cognitive Assessment (MoCA). This test is composed of different subparts and it is highly sensitive to detect MCI. Alternate versions of this test will be randomly assigned ipre- and post-test to each participant, in order to avoid test-retest effects [47]. Executive functions will be assessed through three different tests directed to: inhibition, switching, and working memory respectively. Inhibition processes will be tested with the Stroop test. Participants are seated in front of a computer and requested to indicate the color of the word appearing on the screen by pressing as quickly as possible on the corresponding key of the keyboard while inhibiting the word’s semantic. Four different colors can be presented: green, blue, red, and yellow. Thus, depending on the consistency between the semantic and the color, the condition is considered either congruent (C, e.g., the word “green” written in green) or incongruent (I, e.g., the word “green” written in red). In other trials, “neutral” words (N) are presented (N, e.g., arm, leg...), which are written in one of the different colors. After familiarization with 9 random words, 75 words will be presented for the test. Response times, that is, the time elapsing between the appearance of the word on the screen and manual pressing of the key on the keyboard, will be recorded. Each word remains present on the screen until the response is given. The mean response times (RT, in milliseconds) of the three different conditions will be calculated and compared between the others. Values above the ± 2SD of mean RT will be considered as outliers and excluded. *Switching capacities* will be evaluated through the Trail Making Test (TMT), which is composed of two parts, A and B, respectively. Part A requires participants to draw lines sequentially to connect 25 encircled numbers distributed on a sheet of paper. Part B requires participants to connect alternate numbers and letters (e.g., 1, A, 2, B, 3, C, etc.) with respect to the chronological and alphabetic order [48]. Total execution time (in milliseconds) and the number of errors will be recorded. Switching capacities are quantified by the ratio of the scores obtained in part-B divided by the scores obtained in part-A. Working memory will be assessed with a computerized test developed by the company HappyNeuron™ (Lyon, France), which is composed of two sequential parts. At first, a list of numbers will be provided to the participants via audio-speakers, and subsequently, a list of syllables. Once the full list is played, the participants are asked to repeat the last three items listened. Participants are informed that they cannot ask to listen to the track several times. The test starts with a familiarization trial. The examiner registers the correct answer and goes on with the trials. The time of completion (in seconds) and the total number of points will be recorded. Visuospatial capacities will be tested using the Rey Complex Figure copy task [49]. A complex figure comprising 18 graphic elements, a blank sheet (to copy), and a stopwatch are needed to run the test. The figure is placed in front of the participant, who must reproduce it to the best of his or her ability. The figure is exposed to the subject for a minimum of two and a half minutes and a maximum of five minutes, although it is not removed if the subject exceeds this time. The participant is allowed to copy the figure with a pen, and he/she can self-correct if he/she wants to. After the participant finishes their copy, the figure is removed. The total time required to copy the figure is measured in seconds and the quality of the response is measured for each of the 18 elements that make up the figure. A score between 0 and 2 points is given for each of these elements (maximum score of 36), depending on their accuracy, possible distortion, and location.

### 2.9. Motor Fitness Assessment

Motor fitness will be assessed through tests of balance, gait, functional mobility, flexibility, and motor coordination.

#### 2.9.1. Balance

Two tests of balance capacity will be performed using upright standing, bipedal and unipedal tasks, respectively. Bipedal upright standing will be assessed on a Force platform (AMTI, Advanced Mechanical Technology, Inc., Watertown, MA, USA). After removing their shoes, participants are helped to place their feet apart, to form an angle of 30°, in the middle of the platform. The surrounding environment is standardized, clean, and quiet, to avoid distractions. A red mark is placed on the wall in front of the participants at eye height to help them to concentrate during the eyes-opened trials. Two eyes-open and two eyes-closed trials are performed with 1 min of rest in between. For each trial, the position of the center of pressure (CoP) is recorded (sampling frequency = 100 Hz) as well as the maximum amplitude of oscillation of the center of pressure in mediolateral and anteroposterior directions (mm). In the Unipedal balance test, participants must lift one of their legs and place the foot of the free leg on the knee of the supporting leg [50] and look at a mark placed in front of them, on the wall, at eye height. Then, they are requested to keep a stable equilibrium on their preferred leg for as long as possible. The maximum trial duration is 1 min. One familiarization trial allows deciding the preferred leg to be used. Then, two trials are performed, two eyes-open, two eyes-closed and the best performance of each will be recorded. The time (in seconds) elapsing until equilibrium is lost is measured by the examiner, using the following criterion: arms must be kept along the trunk so that if the participant loses their balance and lifts them more than hip height, the examiner stops the chronometer.

#### 2.9.2. Functional Mobility

The Timed Up and Go (TUG) will be used to assess functional mobility. The participants will sit down on a chair with their feet on the floor and their hands on their legs. At the “go” signal, they have to stand up, walk 3 m at their own pace, firstly as fast as possible and after, turn around the cone, walk back, and sit down again. The performance time will start when the participant starts moving to stand up and it will end when the participant sits down again. Two trials at a self-paced velocity, and two as fast as possible are performed. The duration of the two best trials of the two different conditions will be retained [51].

#### 2.9.3. Flexibility

Hamstring’s flexibility will be tested through the Chair-sit and reach [52]. Participants are asked to sit down on a chair placed against a wall. They will be instructed to extend their preferred leg in front of their hip, with the heel on the floor and the foot dorsiflexed, and to bend the other leg so that the sole of the foot remains flat on the floor. Participants are instructed to reach down the extended leg in an attempt to touch the toes with their fingers of both hands superposed. The position has to be maintained for 3 s and 2 measurements will be performed and the best one kept. The distance (in cm) between the big toe and the hand reached point is measured with a ruler positioned parallel to the lower leg, the big toe will correspond to zero and will be compared with the recommended ranges.

#### 2.9.4. Motor Coordination

Motor coordination will be assessed using the Four-Square Stepping Test (FSST) [53]. The square is created by crossing two 90 cm long scotch tape lines in their middle point, on the floor. The four squares created are numerated with 1 in the high-left square, 2 in the high-right square, 3 in the low-right square, and 4 in the low-left square. To start the trial, the participant stands in square number 1, facing square number 2. Participants must step as fast as possible into each square in the following sequence: 2, 3, 4, 1, 4, 3, 2, and 1, which requires the participant to step forward, backward, and sideways to the right and left with the following instruction: “completing the sequence as fast as possible without touching the drawn lines, with both feet contacting the floor in each square, while facing forward during the entire sequence”. First, the sequence is demonstrated slowly to the participant by the examiner. Then, one familiarization trial is completed to ensure the participant memorized the sequence. Performance is quantified by the time taken to complete the sequence (in sec). The stopwatch starts when the first foot contacts the floor in square 2 and finishes when the last foot comes back to touch the floor in square 1. Two trials will be completed and only the best performance is considered. A trial is repeated if the participant fails to complete the sequence successfully, loses balance, or contacts a line during the sequence. Subjects who are unable to face forward during the entire sequence and needed to turn before stepping into the next square will still receive a score. Participants will be supervised by the examiner and an assistant [53].

#### 2.9.5. Gait Assessment

Gait performance will be evaluated through ten trials of single-task walking (ST) at their preferred speed, on a gait rite (GaitRite system, CIR Systems, Havertown, PA, United States). Participants will start walking and be recorded 2 m before the gait ride beginning line, and stop two meters after in order to avoid integrating acceleration and deceleration. At the end of each trial, participants have the possibility to sit down on a chair to rest, if necessary. Walking speed (cm/sec) and the size of the base of support (cm) will be measured thanks to the software of the GaitRite system.

#### 2.9.6. Dual-Task Assessment (DT)

Dual-task capacities will be evaluated with gait and cognitive tasks performed separately and simultaneously in order to determine the cost of dual-tasking on each function. Three single tasks (ST, two orals, one walking) and two dual-task (DT) conditions, consisting of walking while performing, orally, a cognitive task (i.e., the Trail Making Test, TMT) will be performed. The full procedure is inspired by those proposed by Ho and colleagues [54]. The oral Trail Making Test (OTMT) [55] is composed of two parts: the OTMT part-A (OTMT-A) and the OTMT part-B (OTMT-B). In part-A, participants will be asked to count as fast as possible with the lowest possible number of errors from 1 to 25. In part-B, participants are asked to alternate numbers and letters, starting with 1-A-2-B-3-C…, until the examiner asks to stop. The test is stopped when the participants have given 25 responses. The time of completion and the number of correct responses is recorded. The single gait walking task (ST- described in the gait assessment paragraph, see above) is chosen as a motor task. In the DT conditions, the DT-OTMT-A is performed at first. Participants are asked to perform the OTMT-A task, (procedure described above) while walking at their preferred speed. Then, the OTMT-B task is performed while walking at their preferred speed. Time of completion and the number of correct (number and letters) alternation is recorded (a shift in the sequence of the answers is only considered as an error). By dividing the values recorded for cognitive or gait performances during ST-OTMT-B and DT-OTMT-B by those obtained in the single tasks ST-OTMT-A and the DT-OTMT-A, respectively, a score representing cognitive flexibility is obtained and used as an outcome variable. In order to calculate the DT cost on processing speed, response times measured in DT-OTMT-A are divided by response times measured during the OTMT-A. To calculate the DT cost on mental switching, response times in the DT-TMT-B are divided by response times in DT-TMT-A. The calculation of the cost of cognitive tasks on gait will be done by dividing the score related to walking speed or size of the base of support recorded during the DT walking trial with the same variable recorded in the ST trail.

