### 3.1. Differences in the Effectiveness of the Three Training Protocols on Cognitive, Physical, and Motor Capacities

In accordance with the literature [60,61], global cognitive performance is expected to be enhanced after training in all three groups. However, it is expected that the CT-c and CT-fit protocols will lead to larger improvements in EF than NW. This should result from the combination of the effects of coordination training and aerobic exercise on cognition [10,15] that is allowed by the synergy between facilitation and guidance effects that occur at the brain level [35,62,63]. Moreover, a strong hypothesis is that CT-fit will be a more effective training protocol to improve EFs [64]. It should be the case since the MwT training conditions used in the CT-fit require the implementation of cognition in action, which is closer to real-life situations than TwM task conditions used in the CT-c. Additionally, according to Herold and colleagues [30], MwT training has a higher potential than TwM training to stimulate brain plasticity, due to the multiple sensory systems activated and involved [30]. In summary, one could expect that the CT-fit will show larger benefits for executive function as compared to the other groups. Nevertheless, the two other forms of training are also predicted to lead to improvements in EFs. In addition, due to the presence of specific DT exercises in the CT-c, participants in this training protocol will show better dual-task performance in the related tests. The question remains, however, of the possible benefits of the other protocols on DT performance. This issue will be addressed. Finally, visuospatial capacities are expected to be more improved by the CTs, especially by the CT-fit due to the embodied characteristics, than in NW. Indeed, it has been previously demonstrated that coordination training specifically impacts visuospatial capacities [12,14]. With respect to physical fitness, reflected by cardiovascular capacities, in accordance with [name] and colleagues’ [27] study, it is expected that all three groups will improve their cardiovascular capacities. This could occur if the mean level of effort, indexed by mean heart rate calculated during the different sessions for the three training programs, is roughly equivalent [27]. If not the case, a difference could be observed between the three groups in the relative test. In case of differences between the three groups, we will analyze heart rate and data from the Borg scale to determine whether one of three training protocols was (at least perceived) of higher intensity, relative to the others. Regarding muscular capacities, it is expected that the two CTs will show a significant improvement in the related tests, larger than those observed in NW. Motor fitness is expected to be impacted by the three training programs, as previously observed by [name] and collaborators [27]. However, one expects that the two CTs should be more effective than NW in this respect. Indeed, presumably, NW requires the repetition of automated arm-leg coordination (stabilization by quantitative repetition), while the CT programs allow developing whole-body and multi-limb coordination through a variety of different exercises, which may be learned over the different sessions and could allow qualitative incorporation of new behavioral patterns in the repertoire of existing ones. Thus, NW and CTs are hypothesized to develop motor fitness and coordination capacities [27], while differently, due to the respective part of repetitive practice of automated movements, variety and novelty of the to be learned coordinated movements. In addition, one expects to observe an improvement in walking speed (cm/sec), in the single task in the NW group relative to the CT groups. Additionally, a decrease in the size of the base of support (cm) is expected more for the CTs groups, proving the effectiveness of the specific balance training proposed in these training groups. Finally, as in our previous study, the percentage of responders (i.e., participants who progressed in the exercise under interest) will be also assessed to check whether it is higher for some protocols, though differentially for specific tests. In the lack of related studies available in the literature, no hypothesis is made in this respect but these analyses could help to interpret eventual differences of performance between groups and tests.

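### The index named as the dual-task cost on mental switching divides one dual-task time by another, so it is not a dual-task cost by the section's own standard

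*Protocol article*

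**What the plan says.** Section 2.9.6 (Dual-Task Assessment) has gait and cognitive tasks "performed separately and simultaneously in order to determine the cost of dual-tasking on each function". Three single tasks are planned (oral Trail Making parts A and B, and walking), together with two dual tasks (each oral part while walking). The section then defines four kinds of derived score:

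- **Cognitive flexibility:** part B over part A, separately for single and dual task: "during ST-OTMT-B and DT-OTMT-B by those obtained in the single tasks ST-OTMT-A and the DT-OTMT-A, respectively, a score representing cognitive flexibility is obtained".
- **Cost on processing speed:** "response times measured in DT-OTMT-A are divided by response times measured during the OTMT-A".
- **Cost on mental switching:** "To calculate the DT cost on mental switching, response times in the DT-TMT-B are divided by response times in DT-TMT-A".
- **Cost on gait:** the walking variable "recorded during the DT walking trial with the same variable recorded in the ST trail".

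Section 3.1 predicts that, because CT-c contains specific dual-task exercises, "participants in this training protocol will show better dual-task performance in the related tests". Section 4 (Conclusions) repeats the prediction for CT-c.

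**The concern.** The section's stated aim makes a dual-task cost a comparison of the same task done alone and done while walking. The processing-speed and gait costs follow this. The switching cost does not: numerator and denominator are both dual-task times.

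Two consequences follow from the text itself. First, on response times, one ratio (dual-task B over dual-task A) is reported under two names, once as flexibility and once as a dual-task cost. Second, no dual-task cost on part-B response time exists anywhere in the section, although the single-task part-B time it needs is measured.

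At stake is interpretation. CT-c is expected to do better on dual-task performance, and CT-fit on executive function, which in this protocol includes switching. An index that moves with general switching ability but carries the name of a dual-task cost mixes the two effects that the trial wants to separate.

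**Working it through.** **Reading of the terms.** The switching formula writes DT-TMT. It is read here as DT-OTMT, because the only Trail Making task performed while walking is the oral one. Response times are read as the completion times that the section records.

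**Side by side (Section 2.9.6).**

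| Named quantity | Formula | Type |
|---|---|---|
| Cost on processing speed | DT-A / ST-A | dual / single |
| Cost on gait | DT walking / ST walking | dual / single |
| Cost on mental switching | DT-B / DT-A | dual / dual |
| Cognitive flexibility | ST-B / ST-A and DT-B / DT-A | B / A within condition |

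The third formula matches the second half of the fourth row, not the two costs above it.

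**Algebra, for any times.** Let cA = DT-A / ST-A and cB = DT-B / ST-B be the dual-task costs on the two parts. Then

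DT-B / DT-A = (cB × ST-B) / (cA × ST-A) = (ST-B / ST-A) × (cB / cA).

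So the plan's index:

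1. equals ST-B / ST-A, not 1, when there is no dual-task cost (cA = cB = 1);
2. does not change when both costs fall in the same proportion;
3. rises when cA falls proportionally more than cB, even if both fall;
4. falls when part B gets faster equally in single and dual task, although cB is unchanged.

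**Illustration.** The article gives no oral Trail Making times, so there is no figure of its own to reproduce. Assumed: ST-A 10 s and ST-B 30 s throughout, except that ST-B falls to 27 s in case 3. Assumed costs lie between 1.00 and 1.40. The last column is (DT-B/DT-A)/(ST-B/ST-A) = cB/cA.

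| Case | DT-A (s) | DT-B (s) | Plan's index DT-B/DT-A | cA | cB | cB/cA |
|---|---|---|---|---|---|---|
| No cost at all | 10 | 30 | 3.00 | 1.00 | 1.00 | 1.000 |
| 1 before | 13 | 39 | 3.00 | 1.30 | 1.30 | 1.000 |
| 1 after: equal fall | 11 | 33 | 3.00 | 1.10 | 1.10 | 1.000 |
| 2 before | 12.5 | 40 | 3.20 | 1.25 | 1.333 | 1.067 |
| 2 after: A falls more | 11 | 37.5 | 3.41 | 1.10 | 1.25 | 1.136 |
| 3 before | 12.5 | 40 | 3.20 | 1.25 | 1.333 | 1.067 |
| 3 after: B 10% faster in both conditions | 12.5 | 36 | 2.88 | 1.25 | 1.333 | 1.067 |
| 4 before | 12.5 | 40 | 3.20 | 1.25 | 1.333 | 1.067 |
| 4 after: excess time halved on A and B | 11.25 | 35 | 3.11 | 1.125 | 1.167 | 1.037 |
| 5 before | 14 | 36 | 2.57 | 1.40 | 1.20 | 0.857 |
| 5 after: all cost removed | 10 | 30 | 3.00 | 1.00 | 1.00 | 1.000 |

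Case 1 is a missed improvement. Cases 2 and 5 are improvements that the index shows as worsening. Case 3 is an apparent improvement with no change in cost. In case 4 the index moves the right way, but only from 3.20 to 3.11 while the part-B cost goes from 1.333 to 1.167.

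DT-B / ST-B (column cB) gives the right direction in all five cases. The ratio of ratios cB/cA removes the single-task B/A component, and so corrects case 3. It still stays flat in case 1 and rises in cases 2 and 5.

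**The case against.** **The formula can be read as a sound switching measure.** Section 2.8 quantifies switching on the written Trail Making Test as part B over part A. Staying flat under equal proportional slowing is what any B/A ratio is meant to do, since it takes out general speed. Read as switching ability while dual-tasking, DT-B / DT-A is coherent and only the word 'cost' is wrong. DT-B / ST-B, in turn, mixes general slowing with switching. This stands: part of the choice concerns which construct is wanted. It does not rescue the text, which calls the ratio a dual-task cost and has already defined the same ratio as flexibility.

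**The formula may be a slip** for DT-OTMT-B over OTMT-B. If so, correcting the text settles the point.

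**Stronger readings that the document does not support:**

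- A reader might infer that the CT-c prediction cannot be tested, or will come out reversed. Section 3.1 speaks of related tests in the plural, and the processing-speed and gait costs are properly formed. This is one index among several, and the trial's main question concerns CT-fit.
- A reader might infer that single-task part B goes unused. It enters the single-task flexibility ratio; what is missing is its use in a dual-task cost.
- A reader might take the flexibility sentence to demand gait values from oral-only tasks, or to call DT-OTMT-A a single task. The wording is loose, but it allows gait to apply only where there is walking, and it allows the single-task label to attach to ST-OTMT-A alone.
- The numerical cases show what can happen, not how often or how strongly.

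**Conclusion.** The point holds as a wrong definition: the rule stated for the dual-task cost on mental switching does not measure a dual-task cost by the standard that Section 2.9.6 sets, and on response times it duplicates another outcome. The four algebraic properties hold for any times. They rest only on reading DT-TMT as DT-OTMT and on the two flexibility components being the ratios as written.

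The size in this trial is unknown. Under the assumed times the index ranges from no movement (3.00 to 3.00 while both costs fall from 1.30 to 1.10) to a rise from 2.57 to 3.00 when all dual-task cost is removed. No data are lost, and the other dual-task costs are unaffected. The definition should be settled before results are seen, so that the choice between formulas is not made afterwards.

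**What to change.** Amend Section 2.9.6, or fix the definition in the analysis plan, before analysis:

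1. Define the dual-task cost for part B as DT-OTMT-B / ST-OTMT-B, parallel to the processing-speed cost DT-OTMT-A / OTMT-A.
2. Report DT-OTMT-B / DT-OTMT-A once only, under one name: the switching (flexibility) ratio under dual task.
3. If the extra cost specific to switching is wanted, add (DT-B/DT-A)/(ST-B/ST-A) as a supplementary index, and state that it does not measure overall dual-task cost.
4. Use the OTMT label consistently for the oral test.

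The cost is one formula and a relabelling. All four times are already recorded, so no assessment or data collection changes.
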